### Sample size calculations

The calculations are based on the primary outcomes *OSS, sickness absence percentage, and transfer income percentage.* With 65 participants, who receive physiotherapy exercises, and 65 participants, who do not, a difference in mean *OSS* of 2.4 points can be detected at 12 months with power = 0.8, alpha = 0.05, an assumed standard deviation of 9.0 *OSS* points, a correlation between *OSS* at baseline and follow up of 0.5, and 10% dropout (we expect less than 10% dropout at three months). With 50 participants, who receive occupational medical assistance, and 50 who do not, a difference in mean *sickness absence percentage* of 11.9% can be detected with power = 0.8, alpha = 0.05, an assumed standard deviation of 20%, and up to 10% dropout at three months; the same power is expected for the *transfer income percentage* after 12 and 13–24 months since these outcome measures are based on register information with practically complete follow-up. Power calculations were carried out with STATA 13 software (StataCorp LP, College Station, TX, USA; power pairedmeans and twomeans, respectively).

According to analyses of data from the Danish National Patient Register and the Danish National Register on Public Transfer Payments, around 1150 patients had an arthroscopic subacromial decompression for SIS in Central Region Denmark in 2008, and 67% of these patients had surgery at public hospitals. Thus, we find it realistic to recruit 130 patients within the inclusion period. Originally, we intended to include 400 patients, but with the change of inclusion criteria and outcome measures for the occupational intervention, the necessary sample size was reduced.

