### Statistical analyses

Trial results will be reported as a summary of the outcome measures in each group together with the estimated effect size and its precision. Statistical analyses will be performed according to the intention-to-treat principle, which will be supplemented by per protocol analyses depending on the proportion who do not receive the intended treatment. For outcomes measured using an essentially continuous scale (e.g. *OSS, sickness absence percentage,* and *transfer income percentage*), differences between groups at follow up will be compared by means of linear regression modelling with appropriate transformation of dependent variables. Analyses of effects of the physiotherapy intervention will be adjusted for centre (department of occupational medicine), for the occupational intervention (no, yes, irrelevant), and for the outcome measure at baseline. For the subgroup, who are in paid work for at least 25 hours per week, a two-by-two factorial design will be used. The analyses will focus on main effects of the occupational intervention, but cell-by-cell results will also be reported [22,23]; the analyses will be adjusted for centre. Numbers needed to treat for one patient to benefit from the interventions will be calculated [37]. In addition to main RCT results, supplementary analyses will be performed using variables presented in Table 1.

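### The OSS power figure comes from a one-sample paired calculation; as a two-group comparison the trial detects about 4.1 points, not 2.4, with 80% power

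*Protocol article*

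**What the plan says.** The OSS calculation is in the protocol article under Sample size calculations. The comparison is "With 65 participants, who receive physiotherapy exercises, and 65 participants, who do not", and a difference in mean OSS "of 2.4 points can be detected at 12 months with power = 0.8, alpha = 0.05". The other inputs are "an assumed standard deviation of 9.0" OSS points and a correlation "at baseline and follow up of 0.5, and 10% dropout". The same paragraph gives a detectable difference of 11.9% for the sickness absence percentage, with 50 per group, SD 20% and up to 10% dropout. It then names the Stata routines used: "power pairedmeans and twomeans, respectively". Read in order, the paired-means routine belongs to OSS and the two-means routine to sickness absence and transfer income.

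The section Statistical analyses describes the analysis: "differences between groups at follow up will be compared by means of linear regression modelling". The physiotherapy effect is adjusted for centre, occupational intervention and the baseline value of the outcome. Under Primary outcome measures, OSS is primary for the physiotherapy intervention at both 3 and 12 months.

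**The concern.** A paired-means calculation answers whether the mean within-person change in one sample differs from zero. The trial asks whether patients given physiotherapy end up with better shoulder function than patients not given it. A difference between two independent means has a larger standard error than a mean change in the pooled sample, so a paired calculation on pooled data makes the trial look more sensitive than it is.

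At stake is how the primary physiotherapy result is read. A published claim of 80% power for 2.4 points invites readers to take a non-significant result as evidence against a benefit of that size. If true power for 2.4 points is well under one half, that reading is not justified.

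**Working it through.** **Inputs, all from Sample size calculations:** 65 per group (130 in total), SD 9.0, baseline to follow-up correlation 0.5, alpha 0.05, power 0.80, dropout 10%. Completers: 130 × 0.9 = 117, or 58.5 per group. Sidedness is not stated; two-sided is assumed (step 2 supports this). Results are from the noncentral t distribution unless marked as normal approximation, for which 1.96 + 0.84 = 2.80.

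**Step 1. Reproduce the stated 2.4.**
- SD of the within-person change = 9.0 × √(2 × (1 − 0.5)) = 9.0.
- One paired sample of 117, normal approximation: 2.80 × 9.0 / √117 = 2.33. Noncentral t: 2.35, which rounds to 2.4. Power for 2.4 is 0.82.
- Other paired variants fit less well: 2.23 with 130 pairs, 3.34 to 3.37 with 59 or 58 pairs, and 2.08 one-sided with 117 pairs.

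**Step 2. Check the conventions on the neighbouring figure.** For sickness absence, a two-sided two-sample test with SD 20 and 50 × 0.9 = 45 per group gives 11.94, against the stated 11.9. So the two-sided convention and the handling of dropout are confirmed, and that figure is sound. The problem is confined to OSS.

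**Step 3. Calculate OSS for the planned analysis.**
- Residual SD after baseline adjustment = 9.0 × √(1 − 0.5²) = 7.79.
- Detectable difference, normal approximation: 2.80 × 7.79 × √(2/58.5) = 4.04. Noncentral t: 4.07 (4.05 with 59 per group, 4.09 with 58).
- Power for 2.4 points: 0.38.

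**Step 4. Vary the assumptions.**

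| Two-group variant | Detectable difference | Power for 2.4 |
|---|---|---|
| Baseline-adjusted, two-sided, 58.5 per group | 4.07 | 0.38 |
| Baseline-adjusted, two-sided, no dropout (65 per group) | 3.86 | 0.41 |
| Change score or unadjusted (SD 9.0), two-sided, 58.5 per group | 4.70 | 0.30 |
| Baseline-adjusted, one-sided, 58.5 per group | 3.60 | 0.50 |
| Baseline-adjusted, one-sided, no dropout | 3.42 | 0.54 |

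At correlation 0.5 the cross-sectional SD and the SD of change are both 9.0. Reading 9.0 as the SD of change therefore leaves the paired figure as it is and puts a two-group change-score comparison at 4.7.

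**Step 5. What 2.4 would require.**
- With 58.5 per group, the residual SD would have to be 2.4 / (2.80 × √(2/58.5)) = 4.63. That means a correlation of √(1 − (4.63/9.0)²) = 0.86 instead of 0.5.
- With the stated SD and correlation, n per group = 2 × (2.80 × 7.79 / 2.4)² ≈ 166 completers (167 by noncentral t). Dividing by 0.9 gives 185 to 186 per group, or 370 to 372 randomised.

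**The case against.** The arithmetic is not in dispute; the objections concern what follows from it.

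- **2.4 points is not declared a target.** The article presents it as what the available numbers can detect and states no minimal important difference. This stands. The document shows that the detectable difference is misstated, not that a trial able to detect 4.1 points on a 0 to 48 scale is inadequate. The 370 or so patients in step 5 show the size of the gap and are not a required sample size.
- **The reduction from 400 to 130 patients has another stated reason.** The article attributes it to the changed inclusion criteria and occupational outcomes. This stands, and the reduction should not be blamed on the OSS figure. It remains true that the 65 versus 65 comparison is supported for OSS only by the 2.4-point statement.
- **Misreading of a null result is partly guarded against.** Statistical analyses already promises effect sizes with their precision. This stands in part: a confidence interval helps, but the published power claim would still sit beside it.
- **The route to 2.4 is inferred.** The article names the routine but does not say that 117 was entered as one sample. This is correct, and 117 pairs is only the variant tested that best fits the stated figure. The conclusion does not depend on it, because no two-group variant comes close to 2.4.
- **The other covariates are ignored.** Centre and occupational intervention might explain some variance, but the article gives no figure. Reaching 2.4 would need about 74% of OSS variance explained (0.86²), and baseline supplies 25% (0.5²).
- **It is late.** According to Trial status, the 3-month physiotherapy data are already being analysed. That limits the remedy to correcting the statement, which is all that is asked.

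**Conclusion.** The concern holds. The OSS power statement is wrong for the comparison it describes. With the article's own inputs, the planned two-group baseline-adjusted analysis detects about 4.1 OSS points at 80% power, about 1.7 times the stated 2.4 (4.07 / 2.4), and its power for 2.4 points is about 38%. This rests on a two-sided test, 9.0 as the cross-sectional SD, 10% dropout spread evenly over the groups, and no further variance explained by centre or occupational intervention. Change-score analysis makes it worse (4.7 points, 30%). The most favourable reading, one-sided with no dropout, reaches only 54%. Because OSS is a primary outcome and the error is this large, the statement must be corrected. The planned regression analysis itself is appropriate and is not affected.

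**What to change.** Replace the paired-means calculation for OSS with a two-sample, baseline-adjusted one. Give the residual SD of 7.8 (9.0 × √(1 − 0.5²)), about 58 completers per group, and that the test is two-sided. Restate the result: 65 versus 65 with 10% dropout detects about 4.1 OSS points with 80% power, and power for 2.4 points is about 38%. Correct the software note so that it no longer names the paired routine for OSS. Add one sentence saying that a non-significant physiotherapy result will be interpreted from its confidence interval and not as excluding a 2.4-point benefit.

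The cost is one corrected paragraph and a less favourable published figure. Enrolment, design and analysis stay as they are.

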### Economic evaluation

If the results indicate beneficial effects of any of the interventions, costs and effects will be evaluated and compared from a societal perspective after 12 months, using incremental cost-effectiveness ratios, which will be calculated as the ratio of the change in costs to the incremental effects of the interventions in terms of the primary outcome measures. Additionally, we may use quality-adjusted life-years (QALYs), using the authorised Danish version of the EQ-5D-3L health-related quality of life instrument [38]. Direct total costs of the interventions and usual care in the primary and secondary health care sector will be included, together with direct total costs for patients and their employers. Indirect costs, i.e. costs of health-related productivity loss for the employed subgroup (work-time missed and reduced on-the-job effectiveness) due to health problems, will be assessed by the Work Productivity and Activity Impairment Questionnaire - General Health [39], and the value of the patients’ salaries. Intangible costs will not be assessed separately.

### Trial status

Inclusion of patients without paid work for at least 25 hours per week was terminated by 31 December 2013 (n = 126), and data analysis to evaluate the physiotherapy intervention at 3 months is currently ongoing. Recruitment of patients with paid work for at least 25 hours per week will continue until 30 June 2014.

## Discussion

The few studies that have compared the effect of different postoperative exercise programmes have focussed on the initial 4–12 weeks and have targeted all patients after decompression surgery for SIS [13-16]. We chose to start our interventions 8–12 weeks after surgery, where the six orthopaedic departments that contribute patients to SIP routinely schedule postoperative control, and where we thought that we would be able to target our efforts on the subgroup of patients with continuing shoulder problems and an increased likelihood of chronic disability. Any problems regarding work retention would also be crystallised at this time, where unrestricted activities are usually allowed.

The RCT is embedded in a cohort study, which enables evaluation of selection into the project and reach of the intended target group. It is impossible to blind participants and providers of the interventions. To minimise information bias, we included register-based variables and Constant Score as outcome measures and aimed to ensure blinding of the research physiotherapist. Diagnostic practice, preoperative treatment, indications for surgery, and early postoperative training are not standardised, but preoperative treatment and early postoperative training is described by means of questionnaire data. Moreover, preoperative OSS is assessed, which also ensures that comparability with patients from other settings can be judged.

Results of SIP can be incorporated into clinical practice guidelines for rehabilitation after arthroscopic decompression for SIS. If the interventions are successful, information materials will be prepared for use in hospital departments, primary health care, job centres, and training centres, including job-title-based red-yellow-green charts to guide health care professionals and social workers regarding the need for occupational medical assistance. SIP evaluates a new rehabilitation approach, where physiotherapy and occupational interventions are provided in continuity of surgical episodes of care. If successful, the project may serve as a model for rehabilitation of surgical shoulder patients.

## Abbreviations

EQ-5D-3L: Euroqol-5 dimensions-3 levels; JEM: Job exposure matrix; OSS: Oxford Shoulder Score; QALYs: Quality-adjusted life years; RCT: Randomised controlled trial; SIP: Shoulder Intervention Project; SIS: Subacromial impingement syndrome.
